### Participant entry

A total of 320 participants will be recruited into the trial: 160 participants in each of the two treatment arms. See Fig. 1 for the planned flow of participants through the trial and Additional file 2 for the SPIRIT checklist.

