### Recruitment

Recruitment centres at the Universities of Oxford and Nottingham (United Kingdom) will recruit through GP practices. General practice teams review patients with chronic diseases at least annually, which includes enquiry about smoking status and, for smokers, offer of help to quit smoking. Around 20–30 GP practices will search their patient databases for all current smokers with one or more chronic conditions who are due to have an annual review in the new QOF year, beginning in April 2018. GPs will screen the search list to ensure that all those identified are medically appropriate to participate in the trial. Practice staff will write to or send a text message to these patients inviting them to take part. Patients who are interested in taking part will contact the study team by telephone, text message, email or return reply slip.

The study team will carry out preliminary screening and if the patient appears to be eligible, s/he will be asked to attend a baseline assessment at their GP practice to confirm eligibility (see Additional file 3 for enrolment process). A participant information sheet (PIS; see Additional file 4) and baseline appointment confirmation letter will be sent to potential participants.

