### Randomisation and blinding

Participants will be randomised to intervention or control with a 1:1 allocation ratio. A randomisation list will be generated by the trial statistician using the current version of Stata and validated by a second statistician within the Primary Care Clinical Trials Unit (PC-CTU). The randomisation will be stratified by practice and will use varying block sizes to ensure allocation concealment. The randomisation list will then be passed to someone independent of the trial who will create the randomisation envelopes.

Practitioners will randomise patients during the annual review appointment. On the day of the annual review session, a researcher will give each practitioner a set of opaque A5 sealed envelopes, which will contain a colour-coded randomisation card. The envelopes will be numbered in sequence. The GP or practice nurse will only open the randomisation envelope after they have delivered usual care advice on smoking and are satisfied that the patient meets eligibility for the trial, i.e. the patient confirms that s/he is currently a smoker and declines usual care treatment for stopping smoking. The patient is classed as enrolled in the trial only after the randomisation envelope has been opened. The randomisation card inside the sealed envelope will reveal the patient’s treatment allocation to the GP or nurse, but not the patient. The randomisation envelope will be returned to the researcher by the patient after their consultation.

If the patient is no longer a smoker or accepts usual care treatment, practitioners will fill in a patient ineligibility card containing a tick box option to select if they did not randomise and enrol the patient into the trial. The tick box will indicate the reason for non-enrolment, i.e. patient has stopped smoking, patient accepted usual care or any other reason where it is deemed clinically inappropriate. The ineligibility card will be returned to the researcher after the session and the patient will be thanked for their time given to the study and debriefed.

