#### Other analyses

For examining uptake and use of e-cigarettes, we will calculate the proportion of participants who take up the offer of an e-cigarette and the proportion who continue to use them at 2- and 8-month follow-ups. Proportions will be reported using descriptive statistics. Continued use of e-cigarettes will mean either use until complete smoking cessation was achieved or continued use on > 50% days between baseline and follow-up. For changes in nicotine intake, we will calculate the mean change in salivary cotinine concentrations from baseline to 2-month follow-up for each group and the difference and 95% CI will be computed using linear regression with adjustment for GP practice. Assumptions of linear regression will be assessed and if violated a Mann-Whitney test will be adopted and the median (IQR) will be used to summarise the data and difference in medians (95% CI) will be reported.

We will compare the proportion of people who consent to enrolment into the study and complete 2- and 8-month follow-ups. We will examine these outcomes separately at each recruitment centre to assess the generalisability of our recruitment procedures. Proportions will be reported using descriptive statistics and the difference between trial arms and 95% CI will be calculated.

For participants’ views of the programme (assessed by Likert scale questions), we will calculate the total score and compare these by trial arm using linear regression with adjustment for GP practice. Participants’ recall of key points of the consultation (reported as a yes/no variable) will be presented as frequencies and compared between the two arms using a chi-squared test.

Practitioner fidelity to the intervention will be assessed using a rating scale for key elements in the behavioural interventions and summarised as a score. These are descriptive process data and relate only to the intervention group.

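### Recall of the consultation is compared by an unstratified chi-squared test although randomisation is stratified by practice, so the test is valid but mildly conservative if recall varies between practices

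*Protocol article*

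**What the plan says.** Randomisation and blinding fixes the design: 1:1 allocation in blocks of varying size, and "The randomisation will be stratified by practice".

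Primary and secondary analyses carries practice into the models. Reduction and abstinence are analysed by log-binomial regression adjusted for practice, and change in anabasine by linear regression adjusted for practice. Other analyses treats cotinine in the same way. For the participants' views score it will "compare these by trial arm using linear regression with adjustment for GP practice".

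The next sentence deals with recall, a yes/no variable, which is to be "presented as frequencies and compared between the two arms using a chi-squared test". Neither stratification nor adjustment is mentioned, and no reason is given for treating recall differently from the score beside it. The test is named for a named outcome, so the choice is stated here and not simply deferred to a fuller document.

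**The concern.** When arms are balanced within practice, a practice whose patients recall more raises both arms alike, so differences between practices largely cancel from the arm comparison. A pooled chi-squared test computes its variance as if they did not cancel. The standard error is then too large, the test rejects less often than its nominal level, and some power is given up against an analysis stratified as the trial was randomised.

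This needs recall to vary between practices. That is plausible: the Control subsection says usual care differs from practice to practice, and recall should reflect what the practitioner said. At stake is the efficiency of one process comparison, chiefly for items on which the arms differ moderately.

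**Working it through.** **Inputs from the article.** Participant entry: "A total of 320 participants will be recruited into the trial: 160 participants in each of the two treatment arms". Recruitment: "Around 20–30 GP practices will search their patient databases". Taking these as the recruiting practices gives 320/30 ≈ 11 to 320/20 = 16 participants per practice. Allocation is 1:1, blocked within practice.

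**Assumed, because the article gives no value.** Two-sided 5% level for recall; recall of 50% in both arms under the null and 50% v 65% under the alternative; latent (probit-scale) practice ICC of 0 to 0.30.

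**The plan's own figure.** No power is stated for recall. The total of 320 belongs to the two primary outcomes. At 160 per arm and two-sided 0.025, power is 91.5% for reduction (8% v 8% × 2.8 = 22.4%) and 88.7% for stopping (5% v 5% × 3.4 = 17%). At 0.05 it is 93.3% for stopping. This agrees reasonably with the stated 90% and is not affected by the present point.

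**Closed-form check.** Let λ be the latent ICC. At 50% recall, the ICC of the yes/no variable is ρ = (2/π)·arcsin(λ). With exact balance within practice, the true variance of the arm difference is about (1 − ρ) times what the chi-squared test assumes. Hence:

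- Type I error of chi-squared ≈ 2Φ(−1.96/√(1 − ρ)).
- For 50% v 65%, the pooled SE is √(2 × 0.575 × 0.425/160) = 0.0553 and the unpooled SE is √((0.25 + 0.2275)/160) = 0.0546.
- Chi-squared power ≈ Φ[(0.15 − 1.96 × 0.0553)/(0.0546·√(1 − ρ))].
- Stratified power ≈ Φ[(0.15 − 1.96 × 0.0553·√(1 − ρ))/(0.0546·√(1 − ρ))], using the same factor under the alternative as an approximation.

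| λ | ρ | Type I error, chi-squared | Power, chi-squared | Power, stratified |
|---|---|---|---|---|
| 0 | 0 | 5.0% | 77.7% | 77.7% |
| 0.05 | 0.032 | 4.6% | 78.1% | 79.0% |
| 0.10 | 0.064 | 4.3% | 78.5% | 80.4% |
| 0.20 | 0.128 | 3.6% | 79.3% | 83.1% |
| 0.30 | 0.194 | 2.9% | 80.2% | 85.9% |

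**Simulation check.** 20,000 trials per scenario, 20, 25 or 30 practices, near-balanced arms within practice, Pearson chi-squared without continuity correction against Cochran-Mantel-Haenszel (CMH). Ranges are over the number of practices.

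| λ | Type I error, chi-squared | Type I error, CMH | Power, chi-squared | Power, CMH | Points forgone |
|---|---|---|---|---|---|
| 0 | 4.7-5.2% | 4.7-5.1% | 77.6-78.0% | 77.2-77.8% | 0 |
| 0.05 | 4.5-4.7% | 4.9-5.0% | 77.6-78.4% | 78.4-78.8% | 0.4-0.8 |
| 0.10 | 4.1-4.3% | 4.6-5.1% | 78.3-78.6% | 79.7-80.3% | 1.4-1.7 |
| 0.20 | 3.4-3.8% | 4.7-5.1% | 79.4-79.6% | 82.7-83.1% | 3.2-3.5 |
| 0.30 | 3.0-3.1% | 4.8-5.0% | 79.5-80.1% | 85.0-85.5% | 5.2-5.5 |

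The two approaches agree. With recall at 20% in both arms and λ = 0.30, the chi-squared type I error is 3.2-3.5%. For 10% v 70%, both tests have power of about 100% at every λ. Chi-squared power does not fall as λ rises; the loss is the gain that the stratified test makes and the pooled test does not.

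**The case against.** The strongest reply is that a plain chi-squared test is valid here, that recall is an exploratory process measure, and that the loss may be nil. All of that stands. No ICC is given, and every practitioner receives the same online training and, for the intervention advice, a prompt sheet, so between-practice variation could be small. A reader might infer that recall is strongly grouped by practice; the article does not establish that.

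Four further readings are tempting, and the article does not support them.

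- *The false-positive rate is inflated.* It is not. The error is in the conservative direction.
- *The contamination assessment is weakened.* Under Therapeutic visit and Other measures and exploratory outcomes, contamination is judged from what control participants recall, checked against the recordings. It does not rest on this P value.
- *A stratified test would show that the arms heard the same thing.* A non-significant result from either test cannot establish absence of a difference.
- *The plan contradicts itself, or withholds an effect estimate.* The consent and follow-up differences and the Mann-Whitney fallback also carry no stated practice adjustment, so modelled outcomes are adjusted and simpler comparisons are not. Frequencies by arm are promised, so a crude difference follows, and a confidence interval may well be left to the full protocol or analysis plan.

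What remains is narrower. A named test ignores the stratification factor that the neighbouring comparisons use.

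**Conclusion.** The point holds as a minor efficiency matter. The unstratified test is valid but conservative to the extent that recall varies between practices. Over assumed latent ICCs of 0 to 0.30, its true level runs from about 5% down to about 3.0%, and the power forgone for 50% v 65% runs from nil to about 5 points, with 1 point or less at 0.05. These figures depend on the assumed ICC, recall rates and 5% level, and on near-balance within practice. For items separated sharply by design, the conclusion would be the same under either test. The primary outcomes, the Holm-Bonferroni procedure, the sample size and the contamination check are untouched.

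**What to change.** In Other analyses, replace the chi-squared test for recall with a Mantel-Haenszel analysis stratified by GP practice, and report the stratified risk difference (or risk ratio) with a 95% CI beside the frequencies by arm.

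The cost is one line of wording and no new data. Mantel-Haenszel is preferable to a practice-adjusted binary regression here. With 20-30 practice terms and about 11-16 people per practice, a regression may fail to converge for items near 0% or 100% in an arm. The stratified test gives up essentially nothing if practices do not differ: at ICC 0 its simulated power is within half a point of the chi-squared test's.

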### Data handling, record keeping and retention

The trial is being run as part of the portfolio of trials in the Primary Care Clinical Trials Unit (PC-CTU) at the University of Oxford. The data management will be run in accordance with the Trials Unit standard operating procedures (SOPs), which are fully compliant with Good Clinical Practice (GCP). A study-specific Data Management Plan (DMP) will be developed for the trial outlining in detail the procedures that will be put in place to ensure that high quality data are produced for statistical analysis.

A unique trial-specific number and/or code in any database will identify the participants. All data will be directly entered into electronic case report forms (eCRFs). A full pre-entry review and electronic data validation for all data entered into the clinical database will be provided by study-specific programmed checks. All paper data will be locked in secure cabinets and only the researchers will have access to the files. On all trial-specific documents, other than the signed consent, the participant will be referred to by the trial participant number/code, not by name. A separate database will be used to securely store all identifiable patient information required to contact patients and permit follow up. Access to this information will be strictly on a need to know basis.

On completion of the trial and data cleaning, the study documentation will be transferred to a secure, GCP-compliant archiving facility, where they will be held for 5 years. Participants’ identifiable information will be destroyed at the end of the trial. Prior to database lock, the Data Manager and the Trial Statistician will undertake a dataset review. Following this, quality control will be performed on queries relating to critical data items by the Data Manager.

#### Sample handling

Researchers will obtain saliva samples from participants at baseline and 2-month follow-up visits to measure salivary cotinine and anabasine concentrations. Cotinine, a major metabolite of nicotine, has a half-life of approximately 20 h in smokers [67] and is stable at room temperature for up to 12 days [68]. Anabasine, a specific biomarker of tobacco smoke, has a half-life of 16 h [69] and is also stable at room temperature for up to 14 days.

Saliva will be collected in a plastic vial containing a sterile dental roll (Salivette, Sarstedt). The container will be labelled with the patient ID, type of sample, collection date and time, then transported back to the university. Samples will be sent to the laboratory as soon as they are collected, or they may be stored for up to 7 days at room temperature until they are shipped in batches to a laboratory. The laboratory will store and freeze the samples at − 20 °C until there is a sufficient batch for processing. Salivary cotinine and anabasine concentrations will be determined by liquid chromatography-tandem mass spectrometry (LC-MS/MS) assay. If insufficient saliva is available in the sample for both cotinine and anabasine analysis, anabasine will take priority in the assay. All samples will be disposed of by laboratory staff after final analysis.

### Quality assurance procedures

The trial will be conducted in accordance with the current approved protocol, GCP, relevant regulations and standard operating procedures.

Regular monitoring will be performed according to GCP. Data will be evaluated for compliance with the protocol and accuracy in relation to source documents. Following written standard operating procedures, the monitors will verify that the clinical trial is conducted and data are generated, documented and reported in compliance with the protocol, GCP and the applicable regulatory requirements.

An independent Trial Steering Committee (TSC) will provide oversight of all matters relating to participant safety and data quality. The TSC will include at least one independent clinician, an independent statistician and a participant representative. The TSC will be asked to review the trial protocol and will provide expert advice to the Trial Management Group on the trial progress.

A data monitoring committee is not required for this study as it is of low risk and the trial protocol will not be modified based on interim data.

### Patient and public involvement

The study is supported by a patient advisory group who are involved in several aspects of the trial, including the design, management and conduct of the trial through membership of the trial steering committee. Members include active smokers from our target population, smokers trying to quit and ex-smokers, some of whom have used or are currently using e-cigarettes. Additionally, one member of the group is an experienced vaper and will lead the telephone support service that will provide technical support to patients in the trial on e-cigarette use. The group will help develop and review the practical support booklet, online content and lay summaries of the study findings.

### Expenses and benefits

As there is no therapeutic benefit to participants for attending the baseline and follow-up appointments in person at 2 and 8 months, we will pay those participants who attend a reimbursement (£30 voucher) to cover the cost and inconvenience of attending. Patients who are invited to take part in post-follow-up interviews will be reimbursed £20. For participating in interviews, GPs will be reimbursed £80 per hour, practice nurses will be reimbursed £21.96 per hour and members of the vape team will receive £20 reimbursement.

## Discussion

The heart of this intervention is a brief intervention from the GP or practice nurse to patients to advise them that using an e-cigarette is safer than continuing to smoke and may help them cut down their smoking. That their GP or practice nurse believes this to be true would be effectively communicated by a consent procedure that fully outlined the nature of both interventions; however, this would break the trial randomisation. Instead, to reduce contamination, we will inform potential participants that this is a trial about the way practitioners have conversations with people about their smoking. This approach may also reassure people who have no plans to stop smoking that joining the study will not involve them being subject to hectoring to do something they do not want to do. We will ensure that all patients are fully debriefed and are informed about the purpose of the study at the end of the trial with a debriefing information sheet.

If practitioners can be trained to offer advice about e-cigarettes and patients take up this offer, patients at high risk of increased morbidity and mortality from smoking could be helped to reduce their smoking and increase their chances of quitting. For almost all these specified smoking-related conditions, stopping smoking would be the single most effective way to improve health for patients and is likely to reduce health service costs.

## Trial status

Recruitment began in June 2018. At the time of manuscript submission, the trial was still in the recruitment phase, with 243 participants recruited as of 1st April 2019.

At the time of manuscript resubmission, recruitment had finished in May 2019 and the trial was in follow-up. This manuscript is based on version 3.0 (21 May 2019) of the study protocol.

## Data Availability

The study materials supporting this paper are included as additional files.

## Abbreviations

CI: Chief investigator
CO: Carbon monoxide
COPD: Chronic obstructive pulmonary disease
CRF: Case report form
DMP: Data management plan
eCRF: Electronic case report form
FTCD: Fagerstrom test for cigarette dependence
GCP: Good clinical practice
GDPR: General Data Protection Regulation
GP: General practitioner
HRA: Health Research Authority
LC-MS/MS: Liquid chromatography-tandem mass spectrometry
NCSCT: National centre for smoking cessation training
Ng/ml: Nanograms per millilitre
NHS: National health service
NICE: National Institute for Health and Care Excellence
NIHR: National Institute for Health Research
NRT: Nicotine replacement therapy
PC-CTU: Primary care clinical trials unit
PHE: Public Health England
PIS: Patient information sheet
ppm: Parts per million
QOF: Quality and outcomes framework
RCT: Randomised controlled trial
REC: Research ethics committee
SAE: Serious adverse event
SMI: Serious mental illnesses
SSS: Stop smoking services
SOP: Standard operating procedure
TSC: Trial Steering Committee
